### Ethics and safety

This study is being conducted with University of Miami Institutional Review Board approval. We undergo careful screening to attempt to identify respondents who are not appropriate for the study due to medical concerns that preclude TNP use (e.g., pregnant women, acute cardiac events). During the 1-year duration of the trial, participants may contact the research team in the event of an adverse event. During orientation, participants are advised to seek prompt medical attention in the case of severe side effects from the TNP or other unexpected emergency. Over the course of the intervention and follow-ups, nicotine withdrawal is monitored, in addition to the discussion of medical symptoms.

## Discussion

This RCT is the first to test the efficacy of a group-based, culturally specific CBT among African American smokers. It is also the first study to explore ethno-cultural factors as predictors of the intervention effect. Previous research has attempted to develop and test culturally specific smoking cessation interventions. In this regard, the notion of cultural specificity is not inherently innovative. However, our approach is innovative, as no previous study has adapted CBT to target African American smokers. Second, the CS-CBT is based on theoretical models and existing evidence. Third, we consider the role of individual-difference cultural factors as predictors. And, finally, the rigorous design will allow us to isolate the effect of cultural specificity per se by controlling for possible confounding factors (i.e., treatment intensity and duration). Moreover, the methodological limitations of the extant literature preclude an answer to the fundamental question of whether a focus on ethno-cultural factors has incremental benefits for smokers.

We acknowledge the limitations of this study. The sample consists of treatment-seeking, highly motivated smokers who likely differ from smokers less interested in cessation or those who would not be attracted to group interventions. The sample is also drawn from South Florida, and may not represent smokers in other geographic locations. Thus, we will not be able to generalize to other sub-groups of African American smokers. Study retention is a potential concern, which we attempt to address through incentives and relatively aggressive follow-up strategies (including phone calls, collateral contacts, text messages, mailed letters, and home visits). However, we successfully retained about 70% of African American smokers in a similar group intervention trial using less intensive methods (Webb et al. 2010).

Overall, this trial will answer important, unanswered questions that have the potential to transcend the smoking cessation literature into other areas of health behavior change. If our hypotheses are supported, our culturally specific approach may be used to modify and enhance established traditional intervention approaches, with the ultimate goals of cancer prevention and reducing smoking-related health disparities.

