**Methods/Design:**

A 2-arm randomized controlled trial (RCT) will be conducted to assess the efficacy of a culturally specific group cognitive behavioral therapy (CBT), compared to standard group CBT among treatment-seeking smokers from the community. Participants in both conditions receive the transdermal nicotine patch (TNP) for 8-weeks. We intend to randomize at least 247 adult smokers who self-identify as African American into the trial. Enrolled participants are block randomized into one of two groups: Standard group CBT (control) or a culturally specific group CBT (CS-CBT). Groups are matched for time and attention, and consist of eight sessions. The primary outcome variable is 7-day point prevalence abstinence (7-day ppa). Smoking status is assessed at the end-of-counseling (EOC), and 3, 6, and 12-month follow-ups, with self-reported abstinence verified by saliva cotinine. We hypothesize that the CS-CBT condition will produce significantly greater smoking cessation rates compared to the control condition. We also expect that this effect will be moderated by acculturation and ethnic identity, such that the CS-CBT will show the greatest effect on cessation among participants who are less acculturated and have greater ethnic identity.

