## Design and method

This phase 1 efficacy study is a 2 (intervention) × 4 (time) mixed factorial design with cotinine-confirmed cessation as the primary outcome. Factor 1 is the type of intervention: culturally specific CBT (CS-CBT) versus standard CBT (control), both supplemented by 8-weeks of transdermal nicotine patch (TNP) therapy. CBT in both conditions consists of cognitive and behavioral strategies guided by evidence-based smoking cessation and relapse prevention models (Marlatt & Gordon 1985). The key difference between conditions is whether the intervention is culturally specific. The culturally specific components (e.g., discussion of race and smoking, race-matched clinicians, and an emphasis on religion/spirituality) are those described in the literature and our prior research. Factor 2 is time: End-of-counseling (EOC), and 3, 6, and 12-month post counseling assessments. This study includes a controlled, internally valid, experimental test of the efficacy of CS-CBT among African American smokers. Figure 1 illustrates the flow of participants through the trial.

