**Table 1 Tab1:** **Overview of the interventions**

	CBT	CS-CBT
**Orientation**	Study explanation, structure of sessions and TNP, informed consent, health and smoking, research participation, goal setting, baseline assessment, breath carbon monoxide (CO) and saliva samples.	Same as in the CBT condition. Race and smoking, views on research participation, distrust for biomedical research, concerns about nicotine replacement, goal setting, baseline assessment, breath CO and saliva samples, race-matched clinicians (RMC).
**Session 1**	Review quit plan, positive reinforcement (PR), reasons for quitting, nicotine addiction, introduction to coping response training model, smoking and motivation, TNP use, plan for next 24 hours, behavioral contracting (BC), CO.	Standard CBT. Meaning of being African American, tobacco and African Americans, menthol, RMC.
**Session 2**	Review quit plan progress, PR, benefits of quitting, coping skills, plan for next 24 hours, BC, CO.	Standard CBT. Spirituality and religion in the African American community, RMC.
**Session 3**	Review quit plan progress, PR, stress management, alcohol and smoking, high cost of smoking, plan for next 48 hours, perceived benefits of quitting, BC, CO.	Standard CBT. Stressors unique to African Americans, discrimination and racism, deep breathing exercises, co-morbid addiction, little cigars and blunt use, RMC.
**Session 4**	Review quit plan progress, PR, negative affect and smoking, cognitive restructuring, decision making, plan for next 72 hours, BC, CO.	Standard CBT. Traditional African American values, buddy system, deep breathing exercise, RMC.
**Session 5**	Review quit plan progress, PR, review personal high-risk situations, relapse prevention, responding to lapses, plan for next 72 hours, BC, CO.	Standard CBT. Mood and depression among African Americans, deep breathing exercise, RMC.
**Session 6**	Review quit plan progress, PR, individual high-risk situations, noted benefits of quitting, weight and smoking cessation, minimizing weight gain, relapse prevention, plan for next 7 days, BC, CO.	Standard CBT. Weight and African Americans, smoking and weight concerns (super-gainers), minimizing weight gain (physical activity with limited resources, healthy food choices within soul food diet, recipes), deep breathing, RMC.

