**Session 7**	Review quit plan progress, PR, planning for group termination, a new lifestyle, social support, plan for next 7 days, BC, CO.	Standard CBT. Life in your neighborhood, environmental influences, gaining freedom from smoking, deep breathing exercise, RMC.
**Session 8**	Review quit plan progress, PR, reflect on group experience, long-term trip-ups, review of coping response training, withdrawal, relapse prevention, TNP schedule, follow-up procedures, BC, CO and saliva samples.	Standard CBT. Body as a temple, resources, mobilizing the African American community against the tobacco industry, deep breathing exercise, RMC.

Note: Topics that are not explicitly culturally specific are discussed within this context.

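### Table 1 lists a generic deep-breathing exercise in six of eight CS-CBT sessions and in no control session, so as documented the design tests the CS-CBT package rather than cultural specificity alone

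*Protocol article*

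**What the plan says.** The Discussion of the protocol article states that "the rigorous design will allow us to isolate the effect of cultural specificity per se by controlling for possible confounding factors", and specifies these factors as treatment intensity and duration. The abstract describes the matching behind this claim: "Groups are matched for time and attention, and consist of eight sessions". The Design and method section says: "The key difference between conditions is whether the intervention is culturally specific". Under Intervention conditions, CS-CBT is defined as the standard programme with an added emphasis on African American culture, and its cultural components are listed as deep structure and surface structure.

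In Table 1, each CS-CBT session row opens with the standard CBT label and then lists further items. For session 3 these are "Stressors unique to African Americans, discrimination and racism, deep breathing exercises, co-morbid addiction, little cigars and blunt use, RMC". For session 7 they are "Life in your neighborhood, environmental influences, gaining freedom from smoking, deep breathing exercise, RMC". A note to the table adds that topics not explicitly cultural are discussed in the cultural context.

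**The concern.** To attribute a difference to cultural specificity *per se*, the arms must be alike in every other active ingredient. Matching time and attention equalises how much treatment is given. It does not equalise what is done in that time. Deep breathing is a general stress-coping technique with no cultural content of its own. If it is practised repeatedly in one arm only, a higher abstinence rate under CS-CBT could come from the cultural material, the breathing practice or both. The planned logistic regressions and mixed models estimate the difference between arms, and that difference would contain both parts.

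What is at stake is the interpretation of a positive result. The article offers the trial as an answer to whether attention to ethno-cultural factors adds benefit over an established treatment, and it counts isolation of that effect among the strengths of the design.

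**Working it through.** The plan gives no figure to reproduce. The check is a count in Table 1, followed by a comparison with the article's own list of cultural components.

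**Step 1. Count the sessions naming deep breathing.**

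| Session | CS-CBT row | Control row | Nearest control item |
|---|---|---|---|
| 1 | no: "Meaning of being African American, tobacco and African Americans, menthol, RMC" | no | coping response training model |
| 2 | no: "Spirituality and religion in the African American community, RMC" | no | coping skills |
| 3 | yes | no | stress management |
| 4 | yes | no | cognitive restructuring |
| 5 | yes | no | relapse prevention |
| 6 | yes | no | relapse prevention |
| 7 | yes | no | social support |
| 8 | yes | no | review of coping response training |

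CS-CBT: sessions 3, 4, 5, 6, 7 and 8, which is 6 of 8. Control: 0 of 8. The orientation row names it in neither column.

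**Step 2. Is deep breathing one of the declared cultural components?** The Intervention conditions section lists the deep-structure topics (among them distrust of research, religion, collectivism, racism, menthol and tobacco marketing). It also lists the surface-structure features: race-matched interventionists, inclusive phrasing, and quotations or proverbs. Deep breathing is in neither list. It is also absent from that section's list of control content. By the article's own classification it is not a cultural element, and as written it is not a shared element either.

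**Step 3. Set this against the claim.** Isolation of cultural specificity requires that

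CS-CBT minus control = cultural components only.

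What the article documents is

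CS-CBT minus control = cultural components + repeated breathing exercise.

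The two factors named as controlled, intensity and duration, do not remove the second term.

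**Step 4. Size.** The documents give no effect of deep breathing on abstinence, so the second term cannot be computed. It could be negligible.

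**The case against.** The strongest reply is that Table 1 is headed as an overview, and that the content of the sessions is in detailed manuals that are not shown. Control items such as stress management and coping skills could include breathing practice. The CS-CBT column is also not a clean list of additions: at orientation it repeats goal setting and the baseline samples, and in session 6 it repeats minimising weight gain, which the control row also has. Appearing after the standard CBT label therefore does not prove that an item is exclusive to CS-CBT. This stands. It limits the finding to what is documented, and it makes the remedy depend on what the control manual contains. It does not remove the conflict between table and claim: if the exercise is shared, Table 1 misdescribes the contrast.

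A second reply is the table's note that generic topics are framed culturally, and that breathing first appears beside stressors specific to African Americans. The framing may well be cultural, but the exercise would remain an active ingredient that the control arm is not shown to receive.

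A third is that the Discussion sentence limits itself to intensity and duration. It does name only those two, but the conclusion it draws from controlling them is the broader *per se* one.

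Several stronger readings are tempting, and the documents do not support them:

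- A reader might infer that the trial is confounded as a matter of fact, or that its main comparison is invalid. Absence from an overview is not proof of absence from treatment, and the randomised comparison of CS-CBT with standard CBT stands either way.
- A reader might attach some share of the planned 12-month gap (30% minus 14% = 16 points) to breathing. That gap is a planning assumption and says nothing about this component.
- A reader might add the buddy system in session 4. It sits beside traditional values and may express collectivism, which is a declared cultural element.
- A reader might add that interventionists work in one arm only. That is a stated safeguard against contamination, and race-matching is part of the intervention. The point is separate and is not needed here.
- A reader might want the sentence in Design and method withdrawn. It speaks of the key difference, not the only one, and can stay.

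**Conclusion.** The concern holds as a mismatch between a stated claim and the article's own table. Deep breathing is listed in 6 of 8 CS-CBT sessions and named in 0 of 8 control sessions, and it is not among the declared cultural components. On that documentation, a CS-CBT advantage supports the CS-CBT package and does not support cultural specificity alone.

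This rests on two assumptions: that Table 1 reflects the manuals, and that deep breathing is a generic skill even when taught in a cultural frame. If the first is wrong, what remains is a correction to Table 1. Randomisation, the outcome, the planned analyses and the validity of the comparison between arms are unaffected. The size of any contribution from the exercise is unknown.

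**What to change.** Check the control manual for the breathing exercise and reconcile Table 1 with the Discussion.

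- If the control manual already contains the same exercise, correct Table 1 so that both columns show it. The objection to the *per se* wording on this ground then falls away.
- If it does not, use the same exercise in both manuals for the remaining groups. For groups already treated, state the conclusion as the CS-CBT package versus standard CBT and drop *per se* from the Discussion.

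Correcting the table or the wording costs almost nothing. Aligning the manuals means a revision for groups not yet started. It also leaves earlier and later groups with different content, so results that pool them should keep the package wording. The price of that wording is a narrower claim.
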